### 7.4 Immunogenicity Assessment Indicators

#### 7.4.1 Immunogenicity Blood Sampling Points

- Within 1 hour prior to initiation of IBI362 dosing in Week 1;
- Week 5 (within 1 h before administration on Day 29);
- Week 9 (within 1 h before administration on Day 57);
- Week 13 (168h  $\pm$  12h for Week 12);
- At safety follow-up;
- If a patient withdraws early, an immunogenicity sample should be collected at the early withdrawal visit whenever possible.

#### 7.4.2 Immunogenicity indicators

- Anti-IBI362 antibody (ADA) and neutralizing antibody (NAb) in serum;

## 8. safety reporting and adverse event management

### 8.1 Definition of Adverse Events

An adverse event (AE) is defined as any untoward medical occurrence, whether or not there is a causal relationship with the study drug, in a clinical study subject from the time informed consent form is signed through 90 days after the last dose of study drug, and includes, but is not limited to, the following:

- Exacerbation of pre-existing (prior to clinical study) medical conditions/diseases (including worsening of symptoms, signs, laboratory abnormalities);

- Any newly developed adverse medical conditions (including symptoms, signs and newly diagnosed diseases);
- Clinically significant abnormal laboratory values or results.

## 8.2 Serious Adverse Events Definition of

A serious adverse event is an adverse event that meets at least one of the following criteria:

- Results in death;
- Is life-threatening ("life threatening" is defined as an AE that places the subject at risk of death from the event as it occurred, and does not include an AE that, had it occurred in a more severe form, might have caused death);
- Requires inpatient hospitalization or prolongation of hospitalization, excluding the following:
  - a) Rehabilitation facilities;
  - b) Nursing homes;
  - c) Routine emergency room admission;
  - d) Same-day surgery (e.g. outpatient/same-day/ambulatory surgery);
  - e) Hospitalization or prolongation of hospitalization not associated is unrelated to SAE itself. For example, hospitalization due to original diseases and there are were no new adverse events and aggravation of the original diseases (to check for laboratory abnormalities that persisted even before the study trial); hospitalization for management reasons (e.g. annual routine physical examination); hospitalization during the clinical trial as specified in the study protocol (e.g. procedures required according to the study protocol); and hospitalization that is unrelated to adverse events (e.g. elective surgery); scheduled treatment or surgery, which should be documented in the entire trial protocol and/or the baseline data of the patient; hospitalization only to use blood products.
- Results in persistent or significant disability/incapacity;
- Results in a congenital anomaly/birth defect.

Other important medical events: defined as events that jeopardize the subject or require medical intervention to prevent one of outcomes listed above.. For example, major treatment in the emergency room or allergic bronchospasm at home, cachexia or convulsion without hospitalization, drug dependence or addiction.

## 8.3 Adverse Events of Special Interest (AESI)

The following adverse events are of special interest in this study: allergic

reactions, injection site reactions, elevated transaminases, elevated creatinine, prolonged QTc interval, gastrointestinal reactions (nausea, vomiting, decreased appetite), hypoglycemia, and acute pancreatitis, and severe AEs that are not SAEs related to study drug. In this clinical study, the investigator should pay close attention to whether the patient has the above adverse events and handle them in time.

**The above listed AESIs need to be reported to the sponsor within 24 hours of awareness (i.e. [[contact]](mailto:[contact]) ), if the AESI meets the SAE criteria and is also reported according to the SAE reporting process**

### 8.3.1 Gastrointestinal Reactions

Nausea, vomiting, and diarrhea are adverse events of interest and will be recorded as AEs on the eCRF. Each event will be assessed for severity, length (start and stop date), and relationship to study drug or protocol procedure as deemed by the investigator. (Grading of gastrointestinal reactions 4)

Table 4. Grading of Gastrointestinal Reactions (CTCAE Criteria)

| Gastrointestinal Reactions | CTCAE Grade                                                                                            |                                                                                                                                          |                                                                                                                                                                              |                                              |         |
|----------------------------|--------------------------------------------------------------------------------------------------------|------------------------------------------------------------------------------------------------------------------------------------------|------------------------------------------------------------------------------------------------------------------------------------------------------------------------------|----------------------------------------------|---------|
|                            | Level 1                                                                                                | Grade 2                                                                                                                                  | Grade 3                                                                                                                                                                      | Grade 4                                      | Grade 5 |
| Nausea                     | Decreased appetite without change in eating habits                                                     | Reduced food intake without significant weight loss, dehydration, or malnutrition                                                        | (3) Inadequate intake of energy and water; nasogastric feeding, total parenteral nutrition, or hospitalization required                                                      | -                                            | -       |
| Vomiting                   | No intervention required                                                                               | Outpatient intravenous hydration; medical intervention indicated                                                                         | Need for nasogastric feeding, total parenteral nutrition or hospitalization                                                                                                  | Life Threatening                             | Death   |
| Diarrhea                   | Increase in stool frequency < 4 stools per day compared to baseline; mild increase in ostomy discharge | 4 to 6 stools per day more frequent than at baseline; moderate increase in ostomy output; limiting activities of daily living with tools | ≥ 7 stools per day increase from baseline; hospitalization indicated; severe increase in ostomy output compared with baseline; limiting self-care activities of daily living | Life-threatening; urgent treatment indicated | Death   |

### 8.3.2 Acute Pancreatitis

Serum amylase and/or lipase will be monitored at protocol-specified time points, and additional tests may be added at the discretion of the investigator.

When amylase and/or lipase will be  $\geq 3 \times \text{ULN}$ , further diagnostic evaluation will be required even if the patient will be not symptomatic of acute pancreatitis (Table 5).

Table 5. Patients without symptoms of pancreatitis will be safely monitored by pancreatic enzyme-related indicators  
(Applicable when serum lipase and/or amylase are  $\geq 3$  times ULN)

[figure not shown]

1. Symptomatic mainly refers to abdominal pain associated with pancreatitis, severe nausea, vomiting, and other symptoms can also be considered as related symptoms by the investigator.
2. If the investigator believes that a patient has symptoms of acute pancreatitis any time, regardless of whether based on L/A test results, the investigator should consult a specialist for evaluation, management, assessment of the cause of pancreatitis, discontinuation of dosing and notification of the sponsor.
3. Either or both of lipase and amylase can be used as the evaluation criteria of this algorithm.
4. The optimal time for abdominal imaging is immediately after the enzyme elevation has just been detected. If the investigator or imaging physician judges that it is safe, it is best to use enhanced abdominal CT for examination, or MRI.
5. At a minimum, liver function tests, triglycerides, and ionized calcium levels will be performed and all concomitant medications will be recorded.
6. Negative and positive imaging results are used to indicate acute pancreatitis.

### 8.3.3 Hepatic dysfunction events

If abnormal AST and/or ALT levels are complicated by abnormal elevation of total bilirubin levels, drug-induced liver injury will be considered if the following conditions are met and there is no other cause for liver injury. Such situations should always be considered important medical events.

Table 6 Hepatic Impairment to be Reported as an SAE

| Baseline Period  | Normal (AST/ALT and total bilirubin)                                                                                                                                | Abnormal (AST/ALT and total bilirubin)                                                                                                                |
|------------------|---------------------------------------------------------------------------------------------------------------------------------------------------------------------|-------------------------------------------------------------------------------------------------------------------------------------------------------|
| Treatment period | ALT or AST $\geq 3 \times \text{ULN}$
With total bilirubin $\geq 2 \times \text{ULN}$
AND alkaline phosphatase $\leq 2 \times \text{ULN}$
And no hemolysis | AST or ALT $\geq 8 \times \text{ULN}$
With total bilirubin increase $\geq 1 \times \text{ULN}$ or total bilirubin value $\geq 3 \times \text{ULN}$ |

Patients should return to the study site for evaluation as soon as possible (preferably within 48 hours) after acknowledge of the abnormal results. Assessments should include laboratory tests, detailed history and physical assessment. The abnormality should be considered the the relationship to liver tumors (primary or secondary).

In addition to repeating AST and ALT, laboratory tests to be performed include albumin, creatine kinase, total bilirubin, direct and indirect bilirubin,  $\gamma$ -glutamyltransferase, prothrombin time/international normalized ratio, and alkaline phosphatase. Detailed history collection should include: history of drinking, acetaminophen, soft drugs, various supplements, traditional Chinese medicines, history of exposure to chemical drugs, family history, occupational exposure, sexual behavior, travel history, history of exposure to jaundiced patients, surgery, blood transfusion,

history of liver or allergic diseases, history of heart disease, history of immune diseases, etc.. Further examinations may also include the detection of acute hepatitis A, B, C and E, liver imaging examination (such as biliary tract), autoantibodies and cardiac ultrasound. If repeated testing still confirms compliance with the laboratory criteria defined in Table 6, the possibility of potential drug-induced liver injury should be considered in the absence of other causes of abnormal liver function tests, without waiting for all etiologic liver function test results. Cases of such potential drug-induced liver injury should be reported as SAEs.

### 8.3.4 Hypoglycemic Events

Hypoglycemia is classified by severity as follows:

- **Severe hypoglycaemia:** refers to a condition where the patient requires the assistance of another person to obtain carbohydrate, glucagon or other rescue measures. Hypoglycaemic episodes may be accompanied by neuroglycaemic symptoms and, in severe cases, precipitate epileptiform convulsions or coma. Such events may not have been documented by blood glucose measurements, but recovery of neurological symptoms as blood glucose returned to normal is sufficient evidence that the event is caused by hypoglycemia.
- **Documented symptomatic hypoglycemia:** typical symptoms of hypoglycemia with a plasma glucose concentration less than or equal to 70 mg/dL (3.9 mmol/L).
- **Asymptomatic hypoglycaemia:** Asymptomatic hypoglycaemia are not shown with typical symptoms, but with a plasma glucose concentration less than or equal to 70 mg/dL (3.9 mmol/L).
- **Probable symptomatic hypoglycemia:** during the study, the symptoms of hypoglycemia are not accompanied by a plasma glucose determination, but symptoms are presumed to be caused by a plasma glucose concentration less than or equal to 70 mg/dL (3.9 mmol/L).
- **Relative hypoglycaemia:** The typical clinical symptoms of hypoglycaemia reported by a person with diabetes mellitus who considers himself/herself suffering from hypoglycaemia but with a measured blood glucose concentration greater than 70 mg/dL (3.9 mmol/L).

**The investigator will determine whether a hypoglycaemic episode is severe or not based on the need for medical assistance in addition to the intended assistance that the patient normally receives. All hypoglycaemic episodes will be recorded in the hypoglycaemic module of the eCRF and all severe hypoglycaemic episodes must be reported as SAEs.**

### Blood glucose self-monitoring

During the non-inpatient study period, patients will be required to record the self-inspection blood glucose before meals, 2 hours after each meal and at bedtime (7 times in total). These data should be collected and sorted out within 3 days prior to the scheduled clinical visit. The patients will record their self-measured blood glucose daily as instructed, and the complete data of 7 measurements needs to be collected on each day. If the patient fails to complete the data record for one day, the whole data record for 7 times shall be completed in the next day.

8.3.5 Severe adverse events that are related to the study drug and are not serious adverse events, regardless of whether the event is associated with the same organ or system.

#### **8.4 Adverse Events Severity Assessment**

The investigator will judge the severity according to the grading criteria for adverse events issued by the National Institute on Aging (NIA).

- Mild: Awareness of a symptom or sign that is easily tolerated and of minor irritation that does not interfere with normal activity, and that does not require treatment or medical evaluation; symptoms and signs are transient;
- Moderate: An event that causes a low degree of inconvenience or concern to the patient and may interfere with daily activities, but usually improves with simple therapeutic measures; moderate adverse events may cause some functional impairment;
- Severe: The event interrupts the patient's normal daily life and usually requires systemic drug therapy or other therapy, and usually results in disability.

#### **8.5 Causal relationship between adverse events and investigational drug**

The investigator must assess the causal relationship between the study drug and each AE and answer "yes" or "no" to the question "There is a reasonable possibility that the AE occurred due to the study drug".

When it is determined that there is a "reasonable possibility" that an AE is due to the drug, the following factors should be considered:

- Time course. Exposure to suspect drug. Did the subject actually receive treatment with the suspect drug? Is there a reasonable temporal relationship between the onset of the AE and the suspect drug?
- Consistency of known drug properties. Is the AE consistent with previously reported events for the suspect drug (pharmacology and toxicology) or drugs of the same pharmacological class? Is the occurrence of AEs expected from the

pharmacological properties?

- Dechallenge. Did the AE resolve or improve after stopping or reducing the suspect medication?
- No alternatives. The AE cannot be reasonably explained by another pathology, such as underlying disease, other drugs, other intrinsic or environmental factors.
- Rechallenge. Did the AE reappear after the suspect drug was used after stopping?
- There may be other reasons. Can the adverse event not be explained by an alternative etiology, such as underlying disease, other drugs/vaccines, or other host or environmental factors?

When one or more factors are present, the “reasonable possibility” of the AE needs to be considered.

On the contrary, if the above criteria do not apply, if there is no clear evidence of exposure and a reasonable time course, or if any challenge (if performed) is negative or there is another possible cause of the AE, there may be no "reasonable possibility" for a causal relationship.

Based on the above factors, the relationship between the study drug and the AEs or the role in the adverse event is classified into the following two types by the investigator assessment:

- Related, i.e., consider that there is a reasonable possibility that the study drug is associated with the occurrence of an AE: evidence of exposure to the study drug. The temporal sequence between the onset of the AE and administration of the Sponsor product is reasonable. The AE is more likely to be explained by the study drug than by other causes;

- Unrelated, i.e., it is considered that there is not a reasonable possibility that the study drug is related to the occurrence of AE: for example, the patient does not start the study drug; or there is no reasonable temporal relationship between the occurrence of AE and the exposure of study drug; or other factors that may explain the occurrence of AE compared with the study drug.

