### 3.2.3 Discontinuation Criteria

**If any of the following criteria are met, the investigator and the sponsor should immediately initiate a discussion procedure to decide whether to terminate the dose escalation in each cohort.**

- Occurrence of at least one serious treatment-emergent adverse event related to IBI362 (except for expected adverse events related to the pharmacological properties of IBI362, such as hypoglycemia, etc.).
- No less than 4 patients experience symptomatic hypoglycemic events (plasma glucose levels < 3.0 mmol/L) at a specific dose level, and those events are considered to be related to IBI362.
- No less than 2 patients receiving IBI362 experience persistent (more than one week) symptoms of acute pancreatitis.
- No less than 2 patients experience severe IBI362-related, non-serious adverse events at the same dose, regardless of whether the event is associated with the same organ or system.

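### Protocol 8.5 sets two thresholds for a related adverse event and does not say which one prevails

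*Combined protocol and SAP*

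**What the plan says.** Protocol section 8.5 approaches causality in three stages.

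- **The question.** The investigator answers yes or no to: "There is a reasonable possibility that the AE occurred due to the study drug".
- **Guidance on answering it.** Factors such as time course, known drug properties, dechallenge and alternative explanations are listed. "When one or more factors are present", the possibility has to be considered. In the other direction, if a challenge "is negative or there is another possible cause of the AE, there may be no" reasonable possibility.
- **The two recorded categories.** Related opens by restating the reasonable-possibility standard, then asks for exposure, a reasonable time sequence and this: "The AE is more likely to be explained by the study drug than by other causes". Unrelated opens with the absence of a reasonable possibility and gives examples: drug not started, no reasonable timing, "or other factors that may explain the occurrence of AE compared with the study drug".

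The classification is used in several places. Protocol section 3.2.3 lists four criteria for opening a discussion on ending escalation. The first is "Occurrence of at least one serious treatment-emergent adverse event related to IBI362", with expected pharmacological effects excepted. The second counts patients with symptomatic hypoglycaemia, "and those events are considered to be related to IBI362". The fourth counts patients with severe, non-serious, IBI362-related events. Section 8.3 makes severe, non-serious, drug-related events an AESI category. SAP section 6.6.1 tabulates treatment-related AEs (TRAEs), severe TRAEs, TRAEs leading to discontinuation, and related SAEs.

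**The concern.** One binary label carries two thresholds. A reasonable possibility can exist while another cause is the likelier one. Being the likelier explanation is a stricter, comparative condition. With only two categories, there is no intermediate level for events that pass the first test and fail the second.

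The trial's primary objective is safety and tolerability, and the maximum tolerated dose is a primary endpoint defined through the section 3.2.3 criteria. An investigator who follows the Related definition literally will record fewer related events than one who follows the question. The effect is to under-count related events, and two of the criteria have very low thresholds: one event and two patients.

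**Working it through.** The plan gives no figure to reproduce here. The check is a reading of the text, a count and an illustration.

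**1. A test event run through each standard.** Suppose exposure, reasonable timing and a known drug property are present, together with one alternative cause. The percentages are assumed and serve only to rank the two causes.

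| Standard in 8.5 | Drug 40%, alternative 60% | Drug 60%, alternative 40% |
|---|---|---|
| Yes/no question | yes | yes |
| Related definition | not met (40 < 60) | met |
| Unrelated, last clause read literally (another factor may explain) | met | met |
| Unrelated, last clause read as a comparison (another factor explains better) | met | not met |

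The first column is the firm conflict: a yes under the question is not Related under the definition, whichever way the Unrelated clause is read. The second column shows a further overlap, with both categories met, but only if the Unrelated clause is read literally.

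**2. Is there a tie-break?** Nothing in 8.5 ranks the question above the definitions or the reverse. SAP section 5.3 counts an event as related when the relationship is missing. That does not help when an answer has been recorded under one of two standards.

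**3. Where the label is used.** In section 3.2.3, criteria 1, 2 and 4 require relatedness to IBI362. Criterion 3 (persistent pancreatitis symptoms) requires only receipt of IBI362. That is 3 of 4. The thresholds are at least one event (criterion 1), four patients (criterion 2) and two patients (criterion 4).

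**4. Size of one reclassification.** Each cohort has 8 IBI362 patients (section 3.2.1), so one patient is 1/8 = 12.5 percentage points of that cohort's TRAE rate.

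**5. Illustration of the effect on a criterion.** Let p be the per-patient rate of candidate events and f the share classified as related. The documents give neither, so both are assumptions. For 8 patients in one cohort,

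P(at least r) = 1 − Σ(k < r) C(8,k)(pf)^k(1−pf)^(8−k).

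For criterion 4 (r = 2) at p = 0.1:
- f = 1: 1 − 0.9^8 − 8 × 0.1 × 0.9^7 = 1 − 0.4305 − 0.3826 = 0.187
- f = 0.5: 1 − 0.95^8 − 8 × 0.05 × 0.95^7 = 1 − 0.6634 − 0.2793 = 0.057

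Criterion 4 over a range:

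| p | f = 1 | f = 0.75 | f = 0.5 | f = 0.25 |
|---|---|---|---|---|
| 0.1 | 0.187 | 0.116 | 0.057 | 0.016 |
| 0.2 | 0.497 | 0.343 | 0.187 | 0.057 |
| 0.3 | 0.745 | 0.568 | 0.343 | 0.116 |

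For criterion 1, taken as at least 1 of 8 patients at p = 0.1, the chance is 0.570 at f = 1 and 0.337 at f = 0.5. For criterion 2 (at least 4 of 8) at p = 0.3 it is 0.194 and 0.021. The table shows how sensitive low-count criteria are to the classification. It does not predict this trial.

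**The case against.** The best defence is that 8.5 has one named standard, loosely elaborated. Both categories open with the reasonable-possibility wording, and what follows is elaboration, with the Unrelated list offered as examples. The sentence on one or more factors says only that the possibility must be considered, and the sentence on another possible cause is equally hedged. The listed factors already include alternative causes. The closing words of the Unrelated clause suggest an incomplete comparison that would make it the complement of Related.

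Much of this stands. The hedged sentences are guidance and cannot carry the point, and the Unrelated overlap rests on unclear wording. But the Related category does not merely restate the question. It adds a condition that the question lacks, and restating the standard first only places both thresholds under one label.

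Three stronger inferences are tempting and are not supported:

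- **That the label by itself stops escalation or fixes the maximum tolerated dose.** Under 3.2.3 a met criterion starts a discussion with the sponsor, who is not blinded (5.1.2). The dose follows only if exploration is actually stopped. Criterion 1 also excludes expected pharmacological effects, so not every doubtful event bears on it. What remains is that an unmet criterion does not oblige that discussion.
- **That most gastrointestinal, glycaemic or enzyme events have an alternative cause.** The documents do not say so, and they restrict other glucose-lowering drugs (5.3.1).
- **That sites apply different sentences, so related-event rates cannot be pooled.** The trial is multicentre and this is a risk, but nothing shows that it occurred.

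Investigators are also blinded between IBI362 and placebo, so a strict reading lowers related counts in both arms, and all-cause TEAEs and SAEs are tabulated regardless of causality.

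**Conclusion.** Wrong as written: an internal contradiction in the definition of a related adverse event. It affects events for which the drug is a reasonable but not the likeliest cause, and it leaves their classification to whichever sentence is followed. The reach is criteria 1, 2 and 4 of section 3.2.3, the AESI category of severe non-serious related events, and the TRAE and related-SAE tables.

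The conclusion assumes only that a cause can be reasonably possible without being the likeliest. It does not depend on the literal reading of the Unrelated clause or on the assumed rates. The number of events affected is unknown. Correction is worthwhile because the wording can under-count related events in a small trial whose main purpose is safety, and because it is inexpensive to repair.

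**What to change.** Reconcile section 8.5 to one stated test, using the standard of the protocol's own yes/no question in both category definitions:

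- In Related, remove the condition that the drug be the likelier explanation.
- In Unrelated, reword the last clause as the complement of Related, so that a merely possible alternative cause does not by itself make an event unrelated.

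No dose, schedule or escalation threshold changes. The cost is protocol wording and site retraining, and the reported TRAE rate may be somewhat higher than under the stricter definition.
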